### Interventions

The interventions of this single-group study correspond to the 4D, as consequent individual- and tooth-level management approaches/interventions, to be implemented by the external DP, when possible with remote care and only with non-AGP. At the individual level (Fig. 1), homecare approaches include for all patients, instructions on twice-a-day toothbrushing with ≥ 1000 ppm F, and for high-risk patients, increasing the toothpaste’s fluoride concentration and providing general oral-health improvement information; clinical approaches/interventions include 5% NaF varnish at basic management, T1 and T2; if it applies, high-viscosity glass ionomer ART sealants in Occlusal surfaces (under non-AGP conditions), and motivational engagement of patients and parents through the study-specifically designed Short Behaviour Change Tool (SBCT) [29]. The implementation of the SBCT consists of discussing with the parent each behaviour previously assessed as inadequate (Fig. 3). First, setting a goal to be accomplished (e.g. “Do you think you could incorporate at any point during the child’s evening activities toothbrushing using fluoride toothpaste every night?”); then, planning together how best to achieve it and supporting it with a didactic aid (e.g. a tooth-brushing adhesive instructive diagram for the bathroom mirror), and plan for self-monitoring (e.g. calendar to mark the daily activity). Low-risk patients receive the didactic aids but no behaviour change is conducted.

**Fig. 3 Fig3:**
[figure not shown]
Caries OUT short-behaviour-change tool implementation in parents and children

Interventions at the tooth-surface level include only non-AGP (4D) (Fig. 1) and are detailed in Table 1 for primary teeth and in Table 2 for permanent teeth, depending on the caries lesions’ severity and activity status, with AM, NOC and TPOC options.

**Table 1 Tab1:** Caries OUT pandemic-adapted CCI-4D interventions at the tooth-surface level with non-AGP for primary dentition

	4D at the surface level: primary dentition		
ICDAS-merged Epi score	Caries OUT modified-CCI—care options		
Initial caries			
Inactive	AM		
Active	NOC	*Fossae and fissure:*	*Smooth surfaces:*
		*Option 1*: High-viscosity Glass Ionomer ART sealant + 5% NaF (every 3–6 m)	SDF 30–38% (every 6 m)/5% NaF (every 3 m)
		*Option 2:* 30–38% SDF (every 6 m)/5% NaF (every 3 m)	
		*In teeth close to exfoliation*: option 2 (1 time)	
Moderate caries microcavity/shadow			
Inactive	AM	After clinical judgement and *in teeth close to exfoliation*	
	NOC	*Fossae and fissure:*	*Smooth surfaces:*
		*Option 1:* High-viscosity Glass Ionomer ART sealant	*Option 1:* 30–38% SDF (1 time)/5% NaF (1 time)
		*Option 2:* 30–38% SDF (1 time)/5% NaF (1 time)	*Option 2:* High-viscosity Glass Ionomer ART sealant
Active	NOC	*Option 1*: High-viscosity Glass Ionomer ART sealant + 5% NaF (every 3–6 m)	
		*Option 2:* 30–38% SDF (every 6 m)/5% NaF (every 3 m)	
		*In teeth close to exfoliation* option 2 (1 time)	
	TPOC	*If there is a more advanced Moderate lesion and in a High-risk patient*: ART/Hall Technique	
When considered it necessary have a bitewing radiograph taken to assess the depth of the radiolucency and correlate it with the likelihood of dentine infection (in the middle dentine third). Register radiographic score in 2D, and combine it with the clinical score and the individual caries risk to decide in 3D the specific tooth-surface care plan (NOC/TPOC)			
Extensive caries			
Inactive	AM	After clinical judgement and *in teeth close to exfoliation*	
	NOC	High-viscosity Glass Ionomer ART sealant/30–38% SDF (1 time)/5% NaF (1 time)	
Active	NOC	*Option 1*: High-viscosity Glass Ionomer ART sealant + 5% NaF (every 3–6 m)	
		*Option 2:* 30–38% SDF (every 6 m)/5% NaF (every 3 m)	
	TPOC	*Molar teeth*	*Anterior teeth:*
		*Option 1*: Hall Technique	*Option 1*: ART
		*Option 2*: ART	*Option 2*: 30–38% SDF (every 6 m)
		*Option 3*: 30–38% SDF (every 6 m)	
		*In teeth close to exfoliation:* High-viscosity Glass Ionomer ART sealant + 5% NaF (1 time)/30–38% SDF (1 time)	
		*In deep cavities or reversible pulpitis (without other pulp symptomatology):* One-Step Excavation + ART	

If SDF is available in the centre and the parents or the child don’t accept to have it applied on anterior teeth, select an alternate option

In case of dental emergency/endodontic treatment need take an x-ray register the detection in 2D and 3D, and treat/refer, excluding that tooth

*AM* active monitoring, *NOC* non-operative care, *TPOC* tooth-preserving operative care, *ART* atraumatic restorative treatment, *NaF* sodium fluoride, *SDF* silver diamine fluoride

**Table 2 Tab2:** Caries OUT pandemic-adapted CCI-4D interventions at the tooth-surface level with non-AGP for permanent dentition

	4D at the surface level: permanent dentition		
ICDAS-merged epi score	Caries OUT modified CCI—Care option		
Initial caries			
Inactive	AM		
Active	NOC	*Fossae and fissure:*	*Smooth surfaces:*
		*Option 1*: High-viscosity Glass Ionomer ART sealant + 5% NaF (every 3 m)	5% NaF (every 3 m)
		*Option 2:* 30–38% SDF (every 6 m)/5% NaF (every 3 m)	
Moderate caries microcavity/shadow			
Inactive	AM		
	NOC	*Fossae and fissure:*	*Smooth surfaces:*
		*Option 1:* High-viscosity Glass Ionomer ART sealant	*Option 1:* 5% NaF (1 time)
		*Option 2:* 30–38% SDF (1 time)/5% NaF (1 time)	*Option 2:* High-viscosity Glass Ionomer ART sealant
Active	NOC	*Option 1*: High-viscosity Glass Ionomer ART sealant + 5% NaF (every 3–6 m)	
		*Option 2:* 30–38% SDF (every 6 m) (only in molar teeth)/5% NaF (every 3 m)	
	TPOC	*If there is a more advanced Moderate lesion and in a High-risk patient*: ART	
When considered it necessary, have a bitewing radiograph taken to assess the depth of the radiolucency and correlate it with the likelihood of dentine infection (in the middle dentine third). Register radiographic score in 2D, and combine it with the clinical score and the individual caries risk to decide in 3D the specific tooth-surface care plan (NOC/TPOC)			
Extensive caries			
Inactive	AM		
	NOC	High-viscosity Glass Ionomer ART sealant/30–38% SDF (1 time)/5% NaF (1 time)	
Active	NOC	30–38% SDF (every 6 m)	
	TPOC	ART	
	*In deep cavities or reversible pulpitis (without other pulp symptomatology):* One-Step Excavation + careful ART		

In case of dental emergency/endodontic treatment need take an x-ray register the detection in 2D and 3D, and treat/refer, excluding that tooth

*AM* active monitoring, *NOC* non-operative care, *TPOC* tooth-preserving operative care, *ART* atraumatic restorative treatment, *NaF* sodium fluoride, *SDF* silver diamine fluoride

Interventions at both individual-and tooth surface level, will be conducted during the 12-month study period. After the 1-year follow-up (T3), no further interventions will be conducted for the study, but can be conducted separately if the centre decides to.

The strategies to improve adherence to interventions will include phone and text messages of next appointment reminders for parents and children; a remote communication channel with parents to answer questions and to motivate both the parents and the children to follow the study recommendations; reassuring the parents that in the practice the global SARS COV-2 biosafety guidelines including the use of PPE are being strictly followed. These strategies will also be used to promote participant retention and complete follow-up.

### Outcomes

#### Primary health outcome

Mean number of tooth surfaces with avoidance of caries progression (ICDAS-merged Epi severity and/or activity).

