### Sample size and recruitment

The sample size was determined based on the sample size calculated for the previous randomized clinical trial, which was based on Curtis et al. [42]. We decided to use the mentioned study, even though it is on adults, as it is one of the very few available studies that deals with the management of caries using an updated system, similar to CariesCare International, taking into consideration both the care of caries lesions according to their severity and activity status, as well as of the individual caries risk. The results show differences in averages of surfaces with caries progression, between two preventive care schemes. The Whitehead sample size calculation formula was taken into account, with type-I error: 0.05, type II error: 10%, standard deviation 2.5, expected average of the first group 1.3 and expected average of the second group 2.1.

For the current study, as there is no control arm, with the leader team it was decided to include half of the previous RCT sample size. Thus, the sample size calculation of this single-group interventional study corresponded to 206 3–5 and 6–8 years old children, increasing to a total of 258 after including a 25% dropout. As the sample calculation per arm in each centre in the previous study corresponded to 20 participants, in this single-interventional study we are asking each centre to recruit 27 patients. These would correspond to 567 participants in total if the centres [21] finish the study with 27 participants each.

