### Statistical analysis plan

All the baseline and follow-up the individual- and tooth-level data, the parents’ and dentists’ TEI data, and costs’ information will be digitally registered (after training) for each codified patient in each centre keeping data safely stored and with limited access, in a designed data base in Microsoft Excel (2010), that includes data quality assurance by validation of data. The data will be sent to the DMT at each time point. Data will be analysed by an independent statistician. All statistical tests will be two-tailed tests. The level of statistical significance for all two-sided tests will be set at 0.05. Parametric methods will be considered first. Data that do not meet or cannot be transformed to meet parametric assumptions will be analysed by non-parametric methods. Demographic and clinical features of the participants (centre, gender, age, caries risk, pain, filling status, prs/PRS); oral health behaviour, dental care acceptability and costs, as well as caries experience (DMFS and dmfs with the D component using ICDAS-merged Epi) [35] will be described using mean and standard deviation (SD) for quantitative variables and percentages for qualitative variables.

Regarding costs, the providers’ payment model of the centre will be described (Fee-for-service, Capitation, Salary-based and Pay-for-performance) [43]. For the description of costs, these will be converted to the United States Dollar (USD) under the average Market Representative Exchange Rate for the year 2021 (MRER-average).

ANOVA and Kruskal Wallis analyses will be used to compare the baseline characteristics between centres.

The caries risk control (subjects where risk was reduced from high risk or maintained in low risk), and the number of subjects with avoidance of extraction, pain, and failure of restorations/sealants, will be compared between baseline (T0) and 12-month follow-up (T3) examinations using χ^2^.

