For the analyses at the tooth-surface level, we will exclude teeth that needed a treatment involving AGP (endodontic treatment, surgical extraction, etc.). Caries progression has been defined for this study in terms of a change from the decided and delivered tooth-surface level care (T0, after the 4D basic management) to the tooth-surface level status at the 12-month follow-up (T3) (Fig. 2), as follows: (1) from a sound surface to a caries lesion, a sealant, a filling, or a missing tooth; (2) from a sealant to a caries lesion, a filling, or a missing tooth; (3) to a more severe caries score and/or an active status (or remaining active), and (4) from a filling to a caries lesion or a missing tooth. The severity/activity caries progression will be firstly assessed through descriptive analyses (number of subjects/surfaces) and a comparison in the number of active lesions at 1 year versus baseline will be applied (Wilcoxon test or paired *t* test based on results of the Shapiro Wilk normality test). Multilevel logistic regression will also be used for the surface level data analyses, exploring the clustering of surfaces within individuals, to estimate the association among characteristics variables and the outcomes.

Parents’ treatment evaluation inventory: Comparisons of parents’ treatment acceptability will be conducted between participants classified in baseline as low vs. high risk using Independent *t* test.

Dentists’ treatment evaluation inventory: The dentists’ treatment acceptability will be described.

Oral-health related behaviour classification will be compared between assessments (T0, T1, T2, T3) and between high and low-risk patients using *t* test.

The level of significance considered for all tests will be 5%.

Analyses to handle protocol non-adherence and missing data: Data of patients who leave before the end of the study will be handled separately. A *t* test analysis will be conducted to compare the baseline mean number of surfaces with caries experience (ICDAS-merged Epi dmfs/DMFS) [35] of those children who left the study during the 1-year follow-up period with that of those who remained in the study. If they’ve left after T1 and or T2, their parents TEI will be also compared with that of those who remained, as well as the children’s oral-health behaviour classification, and the caries progression.

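### The primary outcome, the sample-size quantity and the before/after test are three different variables, and no confirmatory analysis or reference value is tied to the primary outcome

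*Protocol article*

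**What the plan says.** Primary health outcome: "Mean number of tooth surfaces with avoidance of caries progression", judged on severity and/or activity. No denominator is given.

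Sample size and recruitment: the calculation draws on an adult study, of which the article says "The results show differences in averages of surfaces with caries progression, between two preventive care schemes". The inputs are "type-I error: 0.05, type II error: 10%, standard deviation 2.5", with "expected average of the first group 1.3 and expected average of the second group 2.1". Half of the former randomised trial's size was then kept: 206 children, raised to 258 for dropout.

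Statistical analysis plan: progression is defined per surface "in terms of a change from the decided and delivered tooth-surface level care (T0, after the 4D basic management" and runs to the 12-month examination (T3). Three analyses follow. Progression is described by numbers of subjects and surfaces. Then "a comparison in the number of active lesions at 1 year versus baseline will be applied", by Wilcoxon or paired t test depending on Shapiro-Wilk. Finally, a multilevel logistic regression of surface data relates characteristics to outcomes.

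The opening of Methods/design presents T0 as the baseline examination covering steps 1D to 3D, with basic management (4D) coming after it.

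**The concern.** With no control arm, the trial's conclusion rests on how clearly the primary quantity is defined and estimated. Here the outcome, the quantity that sized the study and the before/after test do not refer to the same variable. Three consequences follow.

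- A count of avoided surfaces depends on how many surfaces a child has as well as on disease. The trial enrols ages 3–5 and 6–8, and the Discussion points to erupting first permanent molars as a reason for that choice, so tooth counts will differ between children.
- The active-lesion count misses progression without activity, such as a sound surface that becomes an inactive lesion, a sealant, a filling or a missing tooth, or an inactive lesion that worsens in severity.
- If the baseline of that test is the pre-care examination, the count falls when lesions are treated, whether or not progression is later controlled.

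The Discussion says positive results would help change the standard of care. A significant fall in active lesions could be read as that positive result.

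**Working it through.** **1. The plan's own figure.** Inputs from Sample size and recruitment: difference 2.1 − 1.3 = 0.8, SD 2.5, 5% type I error, 90% power. The Statistical analysis plan states "All statistical tests will be two-tailed tests".

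n per arm = 2 × [2.5 × (1.960 + 1.282) / 0.8]² = 205.2, rounded up to 206. A one-sided test would give 168 and 80% power would give 154, so neither matches. For dropout, 206 × 1.25 = 257.5, rounded to 258.

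So 206 is exactly one arm of a two-group comparison of progressed surfaces. It was derived neither from the mean of avoided surfaces nor from a paired test of active lesions.

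**2. What 206 gives in a single group.** For the mean number of progressed surfaces with SD 2.5, the 95% CI half-width is 1.96 × 2.5 / √n:

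- n = 206: ±0.34
- n = 258: ±0.31
- n = 567 (21 centres × 27): ±0.21

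These figures make no allowance for clustering by centre.

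**3. The same precision for avoided surfaces.** Avoided = surfaces at risk − progressed. If the two parts are independent (an assumption), SD(avoided) = √(2.5² + SD(at risk)²). The documents do not give SD(at risk), so a range is shown for n = 206:

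| Assumed SD of surfaces at risk | SD of avoided count | 95% CI half-width |
|---|---|---|
| 0 | 2.5 | ±0.34 |
| 5 | 5.6 | ±0.76 |
| 10 | 10.3 | ±1.41 |

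Unless every child has the same number of surfaces at risk, the half-width reaches or exceeds the 0.8 planning difference somewhere in this range.

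**4. Which baseline the active-lesion test uses.** Methods/design puts T0 before 4D care. The Statistical analysis plan labels T0 as after 4D basic management. Tables 1 and 2 allow active lesions to be sealed or restored, and in primary teeth crowned with the Hall technique.

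An illustration with assumed inputs (none is in the documents): 3 active lesions per child at the examination, no effect on untreated lesions. The count at 12 months is 3 × (1 − share treated) + new active lesions.

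- 20% treated, 0.3 new: 2.4 + 0.3 = 2.7, a 10% fall.
- 50% treated, 0.3 new: 1.5 + 0.3 = 1.8, a 40% fall.
- 10% treated, 0.3 new: 2.7 + 0.3 = 3.0, no change.
- 20% treated, 0.6 new: 2.4 + 0.6 = 3.0, no change.
- 20% treated, 0.3 new, baseline taken after basic management: 2.4 to 2.7, a rise.

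The choice of baseline can therefore reverse the direction of the result in the same children. The size of any fall depends on the share treated and on new lesions.

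**The case against.** A reader might infer that no planned analysis addresses the primary question, or that the active-lesion comparison supplies the only test and the only p-value. The documents do not support that. Descriptive counts of progression are planned, and in a single-group study they can estimate the outcome. A multilevel logistic model of surface data is also planned, although for associations rather than effectiveness, and other tests cover secondary outcomes.

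A reader might also infer that the active-lesion test is bound to be significant. That depends on inputs the documents do not give. The illustration shows no change with 10% treated or with more new lesions, and a rise if baseline is post-management.

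The active-lesion count is also not foreign to the outcome. Under the article's definition, a lesion active at T3 on an analysed surface counts as progression, including one that stayed active. It is a core but incomplete component.

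On tooth count, molars erupting after T0 have no T0 status, so nothing shows that they would add to the total. Differences between children at baseline widen the SD but do not bias a single-group description.

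Finally, model family and offset can reasonably be left to a fuller analysis plan. These objections narrow the point. They do not remove the mismatch between the three stated quantities or the two meanings of T0, which are in the article's own text.

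**Conclusion.** The point holds in a limited form. The primary outcome, the sizing quantity and the before/after test are three unaligned variables. The primary outcome is described and modelled for associations, with no confirmatory analysis or reference value attached.

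The reproduction of 206 as one arm of a two-group contrast is exact. The loss of precision for the avoided count, from ±0.34 to about ±0.76 to ±1.41, rests on an assumed SD of surfaces at risk of 5 to 10 and on independence from progression. Any variation in tooth count acts in that direction unless children with more surfaces at risk also progress on correspondingly more of them.

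The concern about treated lesions leaving the count applies only if baseline is the pre-care examination. In that case a significant fall need not show control of progression, and its size cannot be stated from the documents.

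**What to change.** - State the primary outcome as the number of surfaces with progression per child, out of surfaces at risk, from post-basic-management status to T3. This follows the article's own definition and the quantity used for sizing.
- Report the mean and the rate per surfaces at risk with 95% CI, allowing for clustering within child and centre.
- Reconcile the T0 label between Methods/design and the Statistical analysis plan, and name the baseline of each comparison.
- Keep the active-lesion comparison as supportive and descriptive, on surfaces present at both examinations, and show how many surfaces were sealed, filled, shed or excluded.
- Say that 206/258 comes from one arm of a two-group comparison, and give the precision it provides instead: about ±0.34 progressed surfaces at n=206 with SD 2.5, before any centre clustering.

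The cost is an update of the outcome and analysis wording, using data already planned for collection. The trial gives up a before/after p-value as a headline. The revised outcome would still be an estimate without a comparator, and the conclusions should be worded accordingly.

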#### Secondary health outcomes

Proportion of subjects with avoidance of caries progression (ICDAS-merged Epi severity and/or activity).Proportion of subjects with avoidance of caries risk level increase/no control, and avoidance of extraction, pain, failure of the filling/sealant.Proportion of parents and dentists with high dental care process acceptability (measured with TEI).Proportion of children improving oral-health related behaviours.Description of dental care costs.

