### Setting, participants and recruitment

Each centre will define where they will conduct the local single-group interventional study. This can be either in a dental school clinic, in a dental schools’ community/hospital/school children’s clinics, or if these are not available due to the pandemic, in researchers’ private practices. Invitations will be sent to these clinics and upon interest to participate, the centre coordinator will explain the study, its purposes and procedures. When and if the clinics’ authorities accept to take part, corresponding invitation and information about the study will be sent to the participants’ parents (and children), together with written consent forms (Additional file 2). Written assent forms will be included in countries where it is required and also depending on the age requirement (e.g. in Colombia for children over 6 years) (Additional file 3).

The inclusion criteria are children: (1) aged 3–5 and 6–8 years old; (2) generally healthy, and (3) have parental consent and children’s assent (if needed). The exclusion criteria include children who: (1) have major systemic diseases or major mental/physical disability; (2) their family have plans to move during the study timeline, and (3) wear orthodontic appliances. The strategies to reach the target sample size at enrolment, include the motivation of parents through the invitation, explaining the advantages of having their children receiving a caries patient-centred care and risk-based prevention, and that they will be receiving printed didactic aids to improve the child’s oral health behaviours. Children who attend a different dental practice for care during the study period will be excluded.

Written consent forms signed by parents/carers and written assent forms (when these applies) signed by children will be collected from children interested in participating before the dental examination and treatment take place and subjects will be coded to keep confidentiality.

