For 1D, remote combined with in-office assessment will be conducted with parents, including social/medical/behavioural risk factors (6 items); protective factors (3 items), and oral hygiene (3 items) and dietary (5 items) oral-health behaviours [3, 9, 10, 29, 31–34, 36]. Clinical risk factors (5 items) will be assessed in the dental clinic with the children, as 2D assessments. After assessing dental biofilm (Silness and Löe modified, [37]) , the other clinical assessments are conducted after toothbrushing, with the aid of a WHO probe and drying tooth surfaces and/or removing any dental biofilm only with cotton rolls/gauze (without using compressed air/water). Assessments at the tooth-surface level include: (1) caries lesions staging and activity assessment using the visual ICDAS-merged Epi criteria (Sound, Initial, Moderate microcavity/shadow, Extensive) active/inactive [35], and (2) presence and status of fillings (Optimal, Acceptable or Not acceptable) and sealants (Optimal or Not acceptable), modified from Cvar and Ryge [38], and at the tooth-level: (1) missing due to caries; (2) tooth close to exfoliation, and (3) dental sepsis as a clinical consequence of untreated caries, with the PuIpal Involvement-Roots-Sepsis Index (prs/PRS) modified from the PUFA Index [39] with/without toothache. Routine bite-wing radiographs are not included and only used in specific cases based on clinical need, not as part of the study protocol. For 3D, after synthesis of information from steps 1D and 2D the examiner conducts the personalised care plan, jointly with the child’s parent and the external DP. At the individual-level, a designed matrix based on CCI [9] weighs up the risk and protective factors against each other, classifying the patient’s caries risk into low or high, with a respective 9-month or 3-month risk recall interval. Another matrix, taking into account the COM-B behaviour model [29] weighs up the adequate vs. inadequate oral hygiene and dietary habits behaviours against each other, classifying the patient’s oral-health behaviour into adequate, inadequate or very inadequate. The individual-level risk management decisions will include homecare and clinical approaches/interventions, according to CCI and adapted for the pandemic (with non-AGP and including remote appointments when possible), including implementing a short behaviour-change tool. At the tooth-surface level, according to the synthesis of the clinical assessments defined in 2D, the type of care is defined per surface with non-AGP as: none, active monitoring (AM), non-operative care (NOC), tooth-preserving operative care (TPOC), and at the tooth-level as endodontics or extraction [9, 9].

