
T0 and T3 include full 1D, 2D and 3D assessments. For intermediate T1 and T2 follow-ups, in 1D, all receive full oral-health behaviour reassessment, while risk is fully assessed only in patients previously classified as high-risk; in low-risk, only four risk/protective factors are reassessed (twice-a-day toothbrusing with ≥ 1000 ppm F, daily free-sugar intake above 50 g, dental biofilm and presence of new caries lesions). For 2D, all patients are clinically examined only for the latter. Subsequent 3D is derived. If in T1 or T2 the patient’s risk gets classified opposite to their previous assessment, both the recall interval and the reassessment are adjusted accordingly.

Parents’ and dentists’ acceptance of dental care will be assessed by an external researcher at T1, using designed TEI questionnaires (modified from Newton & Sturmey [40]).

Costs will be assessed in terms of duration and number of appointments regarding the type of care received (assessment/reassessment; individual level: risk/behavioral management, recall; tooth-surface level: NOC, TPOC;) and taking into account if the activity has been conducted solely by the examiner/CD, solely by a hygienist or both together, and country-level economic variables will be described [41–43].

Dropout criteria of a child from the study will include: (1) voluntary withdrawal from the trial by the patient/parents; (2) not attending the reassessments and in-office/remote appointments after three phone/message reminders.

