Taking into account that this study will only consider non-AGP procedures, the caries-progression outcome will be assessed with visual criteria by means of ICDAS-merged Epi, drying tooth-surfaces only with cotton/gauze. While some ICDAS initial lesions might be not detected, this modification of the criteria has been successfully used previously to assess caries progression in school settings, demonstrating its practicality and reliability [49].

While tooth-surface caries progression is the primary outcome, individual-caries-risk control, as well as oral health behaviour change and parents’ and dentists’ care acceptability will also be assessed. Oral-health behaviour change is also relevant within the context of increasing, e.g. oral-hygiene and dietary habits, to help in preventing caries [29]. On the other hand, the process acceptability of the adapted-CCI to both parents and dentists will contribute to understanding if the system is feasible [40].

The adapted-CCI homecare and in-office approaches and interventions are safe for clinical use and reduce the risk of SARS-Cov-2. Moreover, international and local biosafety and PPE considerations are in place, reducing ethical concerns for this study.

Finally, the fact that the implementation of this protocol has been planned to be conducted during the current pandemic situation, raises some challenges, on one hand, related to current ethical restrictions of the participating 21 centres, where the only possibility was to conduct the study as a single-group interventional study—losing the comparability with a control group; on the other hand, centres’ local feasibility, such as start, conduct and finish dates, under public health and governmental uncertainties. In this sense, the centres and researchers involved are putting a lot of effort in pursuing it.

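### The behaviour outcome counts only children who improve, so in a single-group study misclassification alone makes it positive; report improved minus worsened instead.

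*Protocol article*

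**What the plan says.** The Secondary health outcomes list contains "Proportion of children improving oral-health related behaviours". It does not mention children who stay the same or get worse.

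Under Baseline and follow-up oral examinations, the risk assessment conducted with parents includes "oral hygiene (3 items) and dietary (5 items) oral-health behaviours", and a matrix weighs adequate against inadequate habits, "classifying the patient’s oral-health behaviour into adequate, inadequate or very inadequate". At T1 and T2 "all receive full oral-health behaviour reassessment", and T0 and T3 carry the full assessment, so every child is due a class at all four visits.

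The Statistical analysis plan section says: "Oral-health related behaviour classification will be compared between assessments (T0, T1, T2, T3) and between high and low-risk patients using" a t test. No other analysis of behaviour change in the whole cohort is described.

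Three further facts matter. Entry does not depend on behaviour: "The inclusion criteria are children: (1) aged 3–5 and 6–8 years old; (2) generally healthy, and (3) have parental consent" (and assent where needed). The Discussion accepts that the single-group design means "losing the comparability with a control group". The Interventions section gives the short behaviour change tool to high-risk children; low-risk children get the didactic aids only.

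**The concern.** A one-way proportion has no natural null value of zero. Any measure with error moves some children up and some down between two visits, and this outcome keeps the first group and drops the second. In a randomised trial the control arm would show how many children move up by chance. Here nothing does.

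The Discussion lists oral-health behaviour improvement among the things to be explored and says that positive results would help change the standard of care. A reported share of, say, one child in five improving would be easy to take as support for the behaviour component, although a tool with no effect could produce the same figure.

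**Working it through.** **Is there a figure to reproduce?** Not for this outcome. The article gives no expected improvement rate, reliability or baseline class shares. Its sample size of 206 was derived for surfaces with caries progression and serves below only as an n for precision.

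**Model with no true change.** Each child has a stable behaviour level T, and visit v gives X_v = √r·T + √(1−r)·E_v, with T and E_v standard normal and errors independent between visits. Then r is the test-retest reliability. X is cut at the 30% and 70% normal quantiles (−0.52 and 0.52), giving class shares of 30/40/30%. Both r and the shares are assumptions.

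**Improved at T3 against T0.** The pair (X_0, X_3) is bivariate normal with correlation r. The share improving is the probability of moving up one class (two such cells, equal by symmetry) plus that of moving up two:

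| r | up one class | up two classes | improved | worsened |
|---|---|---|---|---|
| 0.95 | 2 × 0.0440 | 0.0000 | 8.8% | 8.8% |
| 0.90 | 2 × 0.0618 | 0.0006 | 12.4% | 12.4% |
| 0.80 | 2 × 0.0835 | 0.0053 | 17.2% | 17.2% |
| 0.70 | 2 × 0.0962 | 0.0132 | 20.6% | 20.6% |
| 0.60 | 2 × 0.1045 | 0.0228 | 23.2% | 23.2% |

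Improved equals worsened in every row because X_0 and X_3 are exchangeable when nothing changes. This does not depend on the class shares.

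**Other class shares.** With adequate/inadequate/very inadequate at 33/33/33, 20/50/30 and 50/35/15%, simulation gives 8–9% improved at r = 0.95, 16–18% at 0.80 and 21–23% at 0.60, with improved minus worsened at zero throughout.

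**Why the denominator must be all children.** A child already adequate at T0 cannot improve. If such children were left out, at r = 0.80 the improvers would be 0.172/0.70 = 24.6%. The worseners would be only those going from inadequate to very inadequate, 0.0835/0.70 = 11.9%. The difference would be about +12.7 points with no true change. The balance holds only in the whole cohort.

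**Does the planned comparison share the problem?** No. It uses every child's class, and children were not selected on behaviour. With no true change, the expected change between T0 and T3 is zero. But a comparison of classification does not yield the proportion named as the outcome.

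**Precision of the net measure.** With p_I improved and p_W worsened, SE = √{[p_I + p_W − (p_I − p_W)²]/n}. At n = 206 and p_I = p_W = 0.172, SE = √(0.344/206) = 0.041, so the 95% CI is about ±8 points, ignoring clustering by centre.

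**Risk groups.** Risk at T0 uses some of the same behaviours: twice-daily fluoride brushing and free-sugar intake are named among the risk and protective factors. Suppose T0 risk correlates 0.71 with the observed T0 behaviour score, with r = 0.70 and no effect. The mean class then drifts by +0.14 in high-risk and −0.14 in low-risk children. At correlation 0.5 the drift is ±0.09, and at 0.3 it is ±0.05. The article does not give this correlation.

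**The case against.** **The rule for improving is not defined.** A reader might infer that one upward class crossing, at any visit and without confirmation, counts as improvement. On that reading, 23–41% of children would improve by chance at some visit for r from 0.90 to 0.60. The article does not say this. It fixes no threshold, visit or denominator, and improvement could be scored per behaviour, since the tool addresses each behaviour judged inadequate. Such details may properly sit in the full protocol or SAP. The objection stands against the any-visit figures. It does not rescue the outcome, because any one-way count on a measure with error has a positive expected value under no change.

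**Worsening is counted in the planned analysis.** This is correct, and it means that the plan as a whole is not blind to deterioration. It leaves the named outcome one-sided.

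**The risk-group comparison.** A reader might infer that it is biased in favour of the tool. As worded, it compares classification, not change. In the model at correlation 0.71 and r = 0.70, the mean class at T3 (0 worst, 2 best) is about 0.72 in high-risk and 1.28 in low-risk children, so the group given the tool looks worse. The favourable drift appears only with change scores or before-after tests within a risk group, which the article does not specify, and its size rests on an unknown correlation. What remains is a limit on interpretation: the groups differ at T0 partly by construction, and the tool goes to one of them only.

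**It is a secondary outcome, and the loss of a control group is acknowledged.** Both are true, and both limit the severity.

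**Conclusion.** The point holds in a limited form. The named outcome is a one-way proportion in a study without a control group, so its level cannot be read as behaviour change. With no true change it would be about 9–23% of all children at T3 for reliability between 0.95 and 0.60 and class shares of 30/40/30%, with an equal share worsening. The direction needs only that the measure has some error. The size rests on assumed reliability and class shares and on independent errors between visits; with a very reliable measure it is below 10%.

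The documents do not support saying that the behaviour analysis as a whole is biased, that a loose any-visit rule has been adopted, or that the risk-group contrast will favour the tool. This is a minor to moderate defect in a secondary outcome, and worth correcting because it costs almost nothing.

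**What to change.** Reword the outcome. At T3 against T0, among all children with both assessments, report the numbers and percentages improved, unchanged and worsened, and make improved minus worsened, with a 95% CI, the behaviour outcome. Do not drop children already adequate at T0 from the denominator. State how improving is defined if it is not a move to a better class.

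Add one sentence saying that the high- versus low-risk comparison is descriptive and not an estimate of the tool's effect, because T0 risk is built partly on the same behaviours and only high-risk children receive the tool. Adjusting for T0 class would not fully cure this: in the no-effect model it still leaves a false difference of about −0.03 to −0.12 classes.

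Requiring a better class at both T2 and T3 is optional. It lowers the chance rate to about 6–12% for r from 0.90 to 0.60, but does not remove it, and it discards improvement first seen at T3.

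The cost is wording only, since behaviour is already assessed at T0 and T3. The small downside is a lower headline figure. The net measure removes the chance component that is symmetric between visits. It does not remove a time trend or a shift in how parents answer, which a single group cannot separate from an effect.
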